### Sample size calculation, number of study participants

Depressive symptoms: There are no prior studies that closely align with our study in terms of study population, intervention and measurement instruments. In our view, the chosen reference Bambling *et al*^45^) represents the best available compromise, as it examines a population of depressed patients, employs an alliance-focused supervision approach and uses the BDI-II as a measurement instrument. Accordingly, we assume a higher reduction in BDIII after 20 weeks in MAFT-D compared with TAU of 4.0 BDI-II units with a SD of 7.3 BDI-II units. To detect such an effect with a type I error of .05 (two-sided hypothesis), a power of .90, an intracluster correlation coefficient of 0.05, and a cluster size of 2 patients per therapist on average, we need 76 therapists and 152 patients in total (38 therapists and 76 patients per group, PASS 15, tests for two means in a cluster-randomised design).

Treatment dropout: We expect that MAFT-D will reduce the treatment dropout rate after 20 weeks from 30% to 12.5%, corresponding to an OR of 3.0. The expected dropout rate of 30% for TAU is a conservative estimate based on a recent meta-analysis (35% dropout)^7^ and numbers in our own clinic (n=3.357 depressed patients; 33% dropout). Previous studies on different AFT approaches reported a difference in treatment dropout rates of 17.5% or greater (Bambling *et al*: IG1=6.1%, IG2=3%, CG=35%; Constantino *et al*: IG=0%, CG=27.3%; Muran *et al*: IG=20%, CG1=37%, CG2=46%).^45 46 76^ With identical design effects, 58 therapists and 116 patients per group (116 therapists, 232 patients in total) are needed to detect this difference (PASS 15, test for two proportions in a cluster-randomised design). We expect that 3% of the randomised sample are not part of the full analysis set (oriented on numbers from the trial of Schramm *et al*^77^) due to the lack of any data postrandomisation.^78^ Thus, based on the larger sample size required for dropout, a sample of 120 therapists and 240 patients in total has to be enrolled.

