Based on previous psychotherapy trials,^77 79^ we expect a loss to follow-up of 15% (of therapists with their patients) at postassessment in BDI-II measurement. With the planned number of sample size and the assumed loss to follow-up, we can prove the assumed effect. We assume a non-compliance rate for the (per protocol, PP) BDI-II analysis (eg, failure to complete 12 sessions within 20 weeks, change in antidepressant medication, use of additional treatments) of 35%.

We expect that 20% of patients and therapists decline study participation, and 15% of therapists and 50% of patients do not meet inclusion criteria. Consequently, 178 therapists and 600 patients need to be initially invited in order to assess eligibility in 142 therapists and 480 patients, in order for 120 therapists and 240 patients to participate in the study and finally analyse 116 therapists and 232 patients. To ensure that the target sample size is achieved, up to five additional units may be recruited as a buffer (ie, 40 therapists, 80 patients, 10 supervisors). This precaution is necessary due to the interdependent nature of the units, where unexpected short-notice dropouts could compromise the participation of entire units.

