These analyses will be conducted either in the full analysis set, which is as complete as possible and as close as possible to the intention-to-treat ideal of including all randomised participants,^118^ or in the sample excluding randomised participants who did not receive a single dose (ie, one therapy session). Missing values are implicitly imputed by the chosen model. This allows for a (modified) intention-to-treat analysis, which results in unbiased estimations under the missing-at-random assumption. Missing values for treatment dropout can only be due to both patient and therapist leaving the study.

Sensitivity analysis for primary endpoints: To investigate the robustness of the results of the primary analyses, we will conduct sensitivity analyses with multiple imputation by chained equations as the imputation strategy. Additionally, primary analyses are repeated in the PP sample. Definition PP sample: patients who receive therapy by trained or non-trained and accordingly supervised therapists as intended by their group allocation without protocol deviations. Protocol violations include: (a) patient’s use of non-allowed medications (eg, newly prescribed antidepressant) or not allowed concurrent psychological treatments, (b) less than 12 completed therapy sessions at the end of week 20 (not relevant with respect to the outcome therapy dropout), (c) participants belonging to the IG, but not receiving the intervention in the intended dose, (d) non-compliant completion of assessments (eg, too early or too late). It will be documented (a) whether the protocol violation occurred during or after the study therapy or overlapping and (b) the measurement time point(s) for which the protocol violation is relevant.

Secondary outcomes: Secondary outcomes are examined exploratorily with analogous methods appropriate for the scale level (ie, mixed linear, logistic, ordinal, or Poisson/negative binomial regression). The contrast of the IG versus CG at week 35 of BDI-II changes from baseline of the model of the first primary outcome is used as a result of secondary outcome analysis. Analyses will be conducted up to and including the first follow-up (week 35) and will be repeated at a later time to include the subsequent measurement points (ie, follow-ups 2 and 3).

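### For week-20 BDI-II, the planned imputation shares the primary model's missing-at-random assumption, so their agreement cannot show robustness to departures from it

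*Protocol article*

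**What the plan says.** All references are to the Protocol article. Under Statistical analyses, the first primary outcome (BDI-II change, contrast at week 20) is analysed with a repeated-measures linear mixed model. On missing data the section says "Missing values are implicitly imputed by the chosen model", and it describes the resulting analysis as one "which results in unbiased estimations under the missing-at-random assumption".

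The paragraph on sensitivity analyses opens with its purpose, "To investigate the robustness of the results of the primary analyses", and names the method: "we will conduct sensitivity analyses with multiple imputation by chained equations as the imputation strategy". It then adds: "Additionally, primary analyses are repeated in the PP sample". No analysis is named that departs from missing at random.

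The sample size section supplies the expected amounts. On treatment dropout: "We expect that MAFT-D will reduce the treatment dropout rate after 20 weeks from 30% to 12.5%, corresponding to an OR of 3.0". On missing outcome data: "we expect a loss to follow-up of 15% (of therapists with their patients) at postassessment in BDI-II measurement". The second figure is not split by arm. Under Methods against bias, patients who leave therapy are offered a paid post-assessment (€150).

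**The concern.** A robustness analysis is useful to the extent that it relaxes an assumption the main analysis needs. Here the assumption most open to doubt is that, given the observed data, whether a week-20 BDI-II is missing does not depend on its unseen value. Standard chained-equations imputation keeps that assumption. The per-protocol repeat keeps it too; by excluding patients with fewer than 12 sessions by week 20, it also removes many of the early leavers whose outcomes are in question.

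Two close estimates would then be reported as robustness although the assumption had not been examined. More than one endpoint is affected: the week-20 BDI-II result decides whether the dropout hypothesis is tested confirmatorily or only explored.

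**Working it through.** **Inputs from the sample size section.** BDI-II difference 4.0, SD 7.3, two-sided alpha 0.05, power 0.90, ICC 0.05, two patients per therapist; 240 patients enrolled, so 120 per arm; 15% missing BDI-II at week 20; treatment dropout 30% (TAU) and 12.5% (MAFT-D).

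**The plan's own figure.** Design effect = 1 + (2 − 1) × 0.05 = 1.05. The normal approximation gives 70 patients per arm; 70 × 1.05 = 73.5, or 37 therapists. A t-based calculation with cluster degrees of freedom first reaches 90% at 38 therapists, 76 patients per arm (power 0.902). This matches the plan, so SD 7.3 and design effect 1.05 are a fair basis for a standard error.

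**Do the two planned analyses differ?** A simulation used 1,000 runs, 120 per arm and 20 imputations, with 21.2% missing in TAU and 8.8% in MAFT-D. It was simplified to one follow-up, with baseline as the only covariate, no clustering and no auxiliary variables. Mean estimated effects (negative favours MAFT-D):

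| Scenario | Truth | Likelihood model | Imputation |
|---|---|---|---|
| Missing at random | −3.97 | −3.97 | −3.97 |
| Missing patients 5 points worse, both arms | −4.60 | −3.98 | −3.98 |
| Missing MAFT-D patients 10 points worse | −3.15 | −4.01 | −4.02 |

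Within runs the two estimates differed with an SD of about 0.08 points. They agreed where both were right and where both were wrong.

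**How large a departure changes the conclusion?** Suppose only missing MAFT-D patients are worse than predicted, by δ points. The estimate then falls by δ × (proportion missing in MAFT-D), and significance is lost at

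δ = (observed difference − 1.96 × SE) / (proportion missing in MAFT-D).

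The SE is held fixed, which is an approximation.

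- *15% missing in each arm:* 120 × 0.85 = 102 per arm. SE = 7.3 × √(1.05 × 2/102) = 1.047; threshold 1.96 × 1.047 = 2.05.
- *15% on average, split in the ratio 30:12.5 (assumed):* TAU 0.30 × 30/42.5 = 21.2%, MAFT-D 0.30 × 12.5/42.5 = 8.8%. SE = 7.3 × √(1.05 × (1/94.6 + 1/109.4)) = 1.050; threshold 2.06.
- *Every treatment dropout missing (extreme, assumed):* 30% and 12.5%. SE = 7.3 × √(1.05 × (1/84 + 1/105)) = 1.095; threshold 2.15.

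| Observed benefit | Tipping δ, 15% in each arm | Tipping δ, 21.2% / 8.8% | Tipping δ, 30% / 12.5% |
|---|---|---|---|
| 2.5 | 3.0 | 5.0 | 2.8 |
| 3.0 | 6.3 | 10.7 | 6.8 |
| 4.0 (planned) | 13.0 | 22.0 | 14.8 |

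**The opposite direction.** If missing patients are worse by the same δ in both arms, the true difference is 4.0 + δ × (TAU proportion − MAFT-D proportion) when the missing-at-random estimate is 4.0. With the 21.2% / 8.8% split, δ = 3, 5, 7.3 and 10 gives 4.37, 4.62, 4.90 and 5.24. The planned estimate would then understate the benefit. With equal proportions the common shift cancels.

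**The case against.** The strongest defence is that imputation can use information the mixed model leaves out. The table of measurement time points lists a symptom rating and alliance scores after every session, observer-rated depression and dropout interviews. A check by simulation supports this. Missingness in MAFT-D was driven by a last-session symptom rating with an assumed residual correlation of 0.5, 0.7 or 0.8 with week-20 BDI-II. Analysis without that rating gave −4.67, −4.97 and −5.01, against truths of −3.98, −4.06 and −3.98; imputation with it gave −4.02, −4.06 and −3.97. So the two planned analyses need not coincide, and the imputation is worth keeping. The article names no auxiliary variables, however. Even a rich imputation makes missing at random more credible without testing what happens if it fails.

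A second defence is that a condensed article leaves details to the SAP. That holds for the imputation model: a reader might infer single-level imputation that ignores therapists, but the text does not say so. It does not cover the main point, because the article itself chooses and labels its robustness analysis.

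Third, a reader might take 30% versus 12.5% as the expected missingness. Those are treatment dropout rates. Leavers are offered a paid assessment, the 15% is not split by arm, and it is described as loss of therapists together with their patients, which need not depend on a patient's score. This stands: arm-different missing BDI-II is plausible but not stated.

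A reader might also extend the point to the dropout endpoint. The documents give little support for that. Unreachable patients are classified as dropouts, and a value is missing only if both patient and therapist leave the study.

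**Conclusion.** The concern holds for week-20 BDI-II. No sensitivity analysis named in the article tests the missing-at-random assumption, so agreement among them cannot show robustness to its failure. That is narrower than saying the imputation has no value or that the primary analysis is biased; the documents support neither.

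The size depends on the result. For an observed benefit of 2.5 points, a shift of about 3 to 5 points in missing MAFT-D patients removes significance; for 3.0 points, about 6.3 to 10.7. The planned 4.0-point effect would need about 13 to 22 points, so a result of that size would be hard to overturn. In each range the lower figure assumes 15% missing in MAFT-D and the higher figure 8.8%. All assume SD 7.3, design effect 1.05, 120 patients per arm and a shift in MAFT-D only. The direction is not fixed either: equal worsening in both arms, with more missing in TAU, would make the planned estimate conservative.

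**What to change.** Keep the chained-equations imputation and add a delta-adjusted version for week-20 BDI-II. Shift the imputed values over a prespecified range (for example 0 to 10 points), varied separately in MAFT-D and TAU so that one-arm and common shifts are both shown, and report the tipping point at which the confirmatory conclusion changes. A reference-based version, in which missing MAFT-D patients follow the TAU pattern, is an optional addition. The imputation model should respect clustering by therapist. Missing BDI-II should be reported by arm so that readers can judge which shifts are credible.

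The article says the SAP will be finalised before database lock, so the addition can be made there. It needs no new data. The cost is a little more programming and one more result to report. No change is needed for the dropout endpoint.

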Other biases: Data monitoring will be conducted by the Clinical Study Office Charité Berlin (CTO). In order to minimise potential bias due to video recordings, all therapy sessions will be recorded. The number of theoretical hours and supervision sessions completed will be compared for MAFT-D and TAU therapists. The use of additional treatments of the patients is monitored and analysed (Client Sociodemographic and Service Receipt Inventory, CSSRI^59^). Additional treatments that could influence outcomes, such as newly prescribed antidepressants or psychopharmacological medications, the repeated use of outpatient psychotherapeutic or psychological services (eg, couples counselling exceeding four sessions), or psychiatric or psychosomatic day-patient or inpatient stays, are considered protocol violations. Therapists’ training preferences are analysed as efficiency modifiers. To assure generalisability, we use a multicentre design. To assess selection bias, we will document ineligible persons among patients (basic demographic information, reason for non-participation). Cases of withdrawal who allow the use of their data will be compared with participants who do not drop out regarding baseline differences. We will document reasons for study discontinuation. Incentives are used to reduce missing values in other outcomes (eg, €150 dropout postassessment).

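### The per-protocol BDI-II analysis, offered as a robustness check, selects patients on staying in therapy, which the plan expects to differ by arm, so its agreement with the primary result is not simple evidence of robustness

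*Protocol article*

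**What the plan says.** Under Statistical analyses, the aim of the sensitivity analyses is stated as "To investigate the robustness of the results of the primary analyses". Two are planned. The first is multiple imputation by chained equations. Then: "Additionally, primary analyses are repeated in the PP sample". The PP sample is defined at patient level, as those treated according to allocation and free of deviations. The listed violations include:

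- (a) medication or concurrent psychological treatment that is not allowed;
- (b) "less than 12 completed therapy sessions at the end of week 20 (not relevant with respect to the outcome therapy dropout");
- (c) for MAFT-D participants only, having received less of the training and supervision than planned;
- (d) assessments completed too early or too late.

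Under Methods against bias, newly prescribed antidepressants, repeated use of other psychological services and "psychiatric or psychosomatic day-patient or inpatient stays, are considered protocol violations".

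The sample size section states: "We expect that MAFT-D will reduce the treatment dropout rate after 20 weeks from 30% to 12.5%, corresponding to an OR of 3.0". It also assumes 35% non-compliance for the PP analysis of BDI-II, naming failure to complete 12 sessions as its first example and giving no split by arm.

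**The concern.** A PP sample supports a robustness claim only if the retained patients remain comparable between arms. Criterion (b) keeps a patient for staying in therapy, and the trial is powered on MAFT-D changing how many patients stay. Waiving (b) for the dropout outcome shows that the overlap was noticed there. For BDI-II, where it causes selection, the rule is kept. Criterion (a) also rests on events after randomisation, though the article does not say how often these occur or what prognosis they carry.

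The trial's own rationale gives reason to expect leavers to differ in outcome: the Background links failure to repair alliance ruptures both to worse outcome and to dropout. If MAFT-D holds in therapy patients who would have left under TAU, the retained MAFT-D group includes a type of patient that the retained TAU group lacks. A PP contrast that differs from the primary one could then reflect who was kept rather than fragility of the primary result. A PP contrast that agrees could reflect offsetting selection.

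**Working it through.** **Inputs.** From the sample size section: dropout to week 20 of 30% (TAU) and 12.5% (MAFT-D); BDI-II contrast 4.0, SD 7.3; intracluster correlation 0.05 with 2 patients per therapist; two-sided 0.05, power 0.90; 240 patients, taken as 120 per arm; PP non-compliance 35%. Not in the article, so assumed: f, the share of dropouts who leave before session 12 (equal in both arms), and d, the number of BDI-II points by which excluded patients improve less than retained ones (equal in both arms).

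**1. The plan's own figures reproduce.** Design effect = 1 + (2 − 1) × 0.05 = 1.05.

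- Dropout: (1.960 + 1.282)² × (0.30 × 0.70 + 0.125 × 0.875) / 0.175² = 109.6 per group; × 1.05 = 115.1; rounded up to whole pairs, 116 per group and 232 in total, as stated. The odds ratio is (0.30/0.70)/(0.125/0.875) = 3.0.
- BDI-II: the noncentral t with 2(K − 1) degrees of freedom gives power 0.894 at K = 37 therapists per group and 0.902 at K = 38, hence 76 patients per group and 152 in total, as stated.
- Enrolment: 232/0.97 = 239.2, hence 240.

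**2. Dropouts removed by criterion (b).** 120 × 0.30 × f in TAU and 120 × 0.125 × f in MAFT-D:

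| f | TAU | MAFT-D |
|---|---|---|
| 1 | 36 | 15 |
| 0.75 | 27 | 11.3 |
| 0.5 | 18 | 7.5 |
| 0.25 | 9 | 3.8 |

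The ratio is 0.30/0.125 = 2.4 throughout; the gap is 17.5 percentage points × f. Patients who have not dropped out but had few sessions are also removed, at a rate that is not given.

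**3. Total exclusions need not be unequal.** At f = 1, criterion (b) takes (30 + 12.5)/2 = 21.25% on average and leaves 35 − 21.25 = 13.75% for other reasons. Criterion (c) can remove MAFT-D participants only. TAU at 30 + 5 = 35% and MAFT-D at 12.5 + 22.5 = 35% is compatible with the plan, since (5 + 22.5)/2 = 13.75. The arms would then be equal in size but selected for different reasons.

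**4. Effect of (b) on the BDI-II contrast.** With mean improvement μ in an arm and excluded share q, the retained mean is μ + q × d. The PP contrast is therefore 4.0 + (0.125 − 0.30) × f × d = 4.0 − 0.175 × f × d.

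| d | f = 1 | f = 0.5 |
|---|---|---|
| 10 | 2.3 | 3.1 |
| 5 | 3.1 | 3.6 |
| 0 | 4.0 | 4.0 |
| −5 (early improvers leave) | 4.9 | 4.4 |

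**5. Without equal d.** Suppose staying follows a normal propensity correlated ρ with improvement, and the lowest share q leaves. The retained mean then rises by ρ × 7.3 × φ(z_q)/(1 − q), where z_q is the q-quantile of the standard normal distribution and φ its density. At f = 1 and ρ = 0.3 this is 1.09 in TAU and 0.52 in MAFT-D, so the contrast is 4.0 + 0.52 − 1.09 = 3.4. At ρ = 0.5 it is 1.81 and 0.86, giving 3.0. The order of magnitude is the same.

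**The case against.** **Nothing confirmatory rests on the PP sample.** The confirmatory result is the week-20 contrast in the full analysis set or the set with at least one therapy session. Multiple imputation is planned as well, and no decision rule uses the PP result. This stands, and it limits the point to interpretation.

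**The text may allow handling by time point.** The article will document which measurement points a violation affects, which could mean removing values rather than patients. That is possible, but the PP sample itself is defined as patients without deviations, and the documentation sentence does not alter that definition.

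**A reader might infer that the PP analysis removes far more TAU than MAFT-D patients overall.** The article does not support this. Dropout is defined without a session threshold, and with weekly sessions a patient can complete 12 and still drop out before week 20. Criterion (c) acts only on MAFT-D, so totals may balance.

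**A reader might also infer that the PP result is worthless.** That goes too far. If those excluded do worse, the shift is against MAFT-D, and a PP result that still favours MAFT-D carries information. The difficulty is that the direction is not known in advance.

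**The shift is smaller than sampling error.** With 84 against 105 retained, the standard error is 7.3 × √(1.05 × (1/84 + 1/105)) = 1.1, more than the 0.9 lost at d = 5, f = 1. This is true, but the shift is systematic, and the PP and primary contrasts share most of their patients, so that standard error is not the yardstick for comparing them. Precision is not the issue either: with 35% loss from 116 per arm, about 75 remain and power for 4.0 points is still about 0.91 if the effect is unchanged.

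**Conclusion.** The point holds as a cheap improvement to a supplementary analysis. Under the plan's own dropout hypothesis, criterion (b) selects the BDI-II sample differently by arm, 2.4 to 1 among dropouts provided f is equal in both arms. For differences of 5 points in either direction, an assumed contrast of 4.0 would appear as anything from about 3.1 to 4.9. These sizes rest on f and d, neither of which the article gives, so no single percentage attenuation should be quoted. Agreement or disagreement between the PP and primary results therefore cannot be read simply as robustness. The documents do not support the stronger conclusions that TAU necessarily loses more patients in total, that the PP result carries no information, or that the primary result or the sample size is compromised.

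**What to change.** In the statistical analysis plan, which is to be finalised before database lock:

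1. Label the simple PP comparison of BDI-II supplementary, and report exclusions by arm and by reason, with (a) to (d) shown separately.
2. Base the question of what would have happened had patients complied on all randomised patients. Rerun the primary BDI-II model with values after the violation set to missing. Include the session-5 BDI-II as a further repeated measurement, not as a covariate, and keep the time-by-group term in this run so that the week-20 contrast is not averaged with session 5. Alternatively, weight compliant patients by the inverse probability of compliance, estimated within arm.
3. Keep this analysis beside the planned multiple imputation, not in its place.

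The cost is some wording and one extra model run. The session-5 BDI-II is already in the assessment schedule, and the timing of violations is already to be documented. The downside is that the analysis relies on missing at random given earlier BDI-II values, an assumption that the primary model also makes, and patients who leave before session 5 contribute only their baseline. It answers the compliance question with less selection, but does not test that assumption.

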### Psychotherapy training

TAU-D and MAFT-D therapists will continue to participate in their regular training courses. Group supervisions of treatments will be carried out by experienced supervisors either with MAFT-D specific focus or according to the usual procedure. Supervision frequency and format (one session for every four therapy sessions, in person, additional individual supervision is permitted in accordance with the regulations of the specific institute in the event of crises or for questions regarding the report for the health insurance company) represents the common standard and legal requirement for trainee therapists in our country. This frequency might deviate from other clinical trials or the clinical practice in other regions. The supervision frequency may influence outcomes but also reflects local real-world practice conditions, adding ecological validity to the study. The supervision groups are fixed, and in order to participate, the therapist must have already started at least one study therapy. Group supervisions will occur monthly or biweekly, with patients being discussed for varying amounts of time (10–50 min per case). Supervisors will receive regular supervision fees. The hours of the workshop for the MAFT-D group will replace other non-mandatory courses of the regular training.

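### The per-protocol waiver for the dropout outcome covers the session minimum but not the MAFT-D dose rule, so the PP dropout comparison can lean towards MAFT-D

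*Protocol article*

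**What the plan says.** All of the PP text is in the protocol article, section Statistical analyses, under the sensitivity analysis for the primary endpoints.

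- **Scope.** "Additionally, primary analyses are repeated in the PP sample". This covers both BDI-II change and therapy dropout at 20 weeks.
- **General definition.** The PP sample consists of patients treated by therapists who were trained or not trained, and supervised, as their allocation intended, without protocol deviations. This sentence covers both arms. The list of violations that follows is introduced as examples, not as a complete list.
- **Criterion (b).** "b) less than 12 completed therapy sessions at the end of week 20 (not relevant with respect to the outcome therapy dropout". It applies to both arms and is switched off for the dropout outcome.
- **Criterion (c).** "c) participants belonging to the IG, but not receiving the intervention in the intended dose". It names one arm and has no waiver. The article does not quantify the intended dose.
- **The word dose.** Just before, the modified intention-to-treat option is described as analysis "in the sample excluding randomised participants who did not receive a single dose (ie, one therapy session").

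The section Psychotherapy training sets how supervision accrues: "one session for every four therapy sessions, in person", in groups that meet monthly or biweekly, and "in order to participate, the therapist must have already started at least one study therapy".

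**The concern.** When leaving therapy is the outcome, an exclusion rule that depends on how long the patient stayed removes events. The plan recognises this for (b) and waives it. Criterion (c) is also a dose rule. Supervision follows the therapy sessions held and starts only once a study therapy has begun, so a patient who leaves in the first weeks may have had little or no MAFT-D-supervised treatment, and may have had little because they left. Under (c) such an IG patient can be excluded. A TAU patient who leaves at the same point meets no dose rule stated for that arm.

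The PP repeat is meant to show whether the primary results are robust. A dropout comparison that loses events from one arm could appear to confirm a MAFT-D benefit that is not there, or enlarge one that is.

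**Working it through.** **1. The plan's own figure.** The section on sample size states that "MAFT-D will reduce the treatment dropout rate after 20 weeks from 30% to 12.5%, corresponding to an OR of 3.0". It uses two-sided alpha 0.05, power 0.90, an intracluster correlation of 0.05 and two patients per therapist, and arrives at 116 patients per group.

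- Design effect: 1 + (2-1) × 0.05 = 1.05.
- Unpooled two-proportion formula: (1.960 + 1.282)² × (0.30 × 0.70 + 0.125 × 0.875) / 0.175² = 109.6 per group.
- 109.6 × 1.05 = 115.1, that is 58 therapists with two patients each, or 116 per group. The figure reproduces.
- Odds ratio (TAU/MAFT-D): (0.30/0.70) / (0.125/0.875) = 3.0. This also reproduces.

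**2. What criterion (c) does to the PP odds ratio.** Let p be the IG dropout rate, n the IG size, f the share of IG dropouts removed by (c) and h the share of IG completers removed by (c). Neither f nor h is in the document; both are assumptions.

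- IG odds in the PP set: np(1-f) / [n(1-p)(1-h)].
- The IG odds, and so the odds ratio MAFT-D/TAU, are multiplied by (1-f)/(1-h).

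**3. No true effect.** Take 30% dropout in both arms (the plan's TAU rate) and 116 per arm, so 34.8 dropouts and 81.2 completers are expected in the IG. The TAU arm is left untouched by (c). The last column is a normal approximation for two proportions, with sample sizes divided by 1.05.

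| f | h | IG dropouts left | IG completers left | IG PP rate | OR MAFT-D/TAU | Chance of two-sided p<0.05 |
|---|---|---|---|---|---|---|
| 0 | 0 | 34.8 | 81.2 | 30.0% | 1.00 | 5% |
| 20% | 0 | 27.8 | 81.2 | 25.5% | 0.80 | about 11% |
| 20% | 10% | 27.8 | 73.1 | 27.6% | 0.89 | about 7% |
| 20% | 20% | 27.8 | 65.0 | 30.0% | 1.00 | 5% |
| 10% | 20% | 31.3 | 65.0 | 32.5% | 1.13 | about 7% |

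Example, second row: 27.8 / (27.8 + 81.2) = 25.5%, and (1-0.20)/(1-0) = 0.80. About seven IG patients (0.20 × 34.8) produce that shift.

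**4. Under the planned effect.** The same factor applies. With f=20% and h=0, the planned odds ratio of 3.0 (TAU/MAFT-D) becomes 3.0/0.80 = 3.75 in the PP set.

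**5. Direction.** The comparison leans towards MAFT-D if f exceeds h, is unbiased if f equals h, and leans towards TAU if h exceeds f. If dose is counted over the patient's own therapy, early leavers fall short more often than completers, so f above h is the expected case. If dose means therapist-level training unrelated to when the patient left, f and h should be similar and the bias small or absent.

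**The case against.** The strongest reply has four parts.

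- **The general PP definition covers both arms.** A TAU patient whose therapist was not supervised as intended can fail it, and the list of violations is not exhaustive. A reader might infer that TAU patients of unsupervised or poorly attending therapists necessarily stay in the PP set, and that the BDI-II comparison is therefore distorted too. The text does not establish either inference. What stands is narrower: the only violation that names a dose of the intervention is listed for the IG, with no explicit parallel in TAU.
- **The intended dose is not defined in the article.** MAFT-D is delivered to therapists, and the threshold may properly be set in the statistical analysis plan. A patient who leaves at session three could be judged to have had all that was due by then. The modified intention-to-treat sentence uses dose for a therapy session, but in all randomised participants, so it does not settle the meaning in (c). It is therefore not documented that early IG dropouts will be excluded, only that they can be.
- **The mechanism is limited.** A therapist needs only one study therapy under way to join supervision and treats two study patients on average. A second patient who starts later may be treated under running supervision from the outset. The plan also records for which time points a violation is relevant.
- **Large effects need strong assumptions.** With h=0, removing half of the IG dropouts would give an odds ratio of 0.50. A reader might take that as the size of the problem. It would need half of all 20-week dropouts to be removed under (c) and not one completer; nothing in the document supports that.

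None of this supplies the missing waiver. The reason for waiving (b) applies equally to (c) whenever dose depends on time in therapy, and no other section says that (c) is set aside for dropout.

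**Conclusion.** The point holds as a conditional one. As written, (c) can remove IG patients from the PP dropout analysis because they dropped out, with no explicit counterpart in TAU, and the bias then favours MAFT-D. It rests on the intended dose being judged by sessions or supervision received during the patient's therapy, and on (c) removing a larger share of IG dropouts than of IG completers.

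The size cannot be taken from the document: it gives neither the timing of dropout nor a dose threshold. Over the illustrated range the null odds ratio lies between 0.80 and 1.00 when f is at least h, and moves above 1 when h exceeds f.

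A reader might also infer that the trial's type I error is inflated. It is not. The primary analyses use the full or modified intention-to-treat set, and the PP repeat is a sensitivity analysis outside the hierarchical test. The sample size is unaffected. What is at stake is how far the PP dropout result can be trusted as a robustness check.

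**What to change.** In the PP definition, and in the statistical analysis plan before database lock:

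1. State that (c), like (b), is not applied for the therapy-dropout outcome. Alternatively, judge (c) only on therapist-level training and supervision that was due before the patient's last session, so that leaving early cannot itself cause exclusion.
2. Word the training and supervision adherence criterion so that it applies in parallel to both arms, in line with the general PP definition. The section Methods against bias already plans to compare supervision sessions completed between MAFT-D and TAU therapists.

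The cost is about one sentence, with no new patients or procedures. The downside is that the PP dropout set keeps some IG patients with little MAFT-D exposure and may lose a few TAU patients.
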